### 3.4. Subgroup Analysis

We will conduct a subgroup analysis of control group participants to assess potential predictors of objective comprehension of abbreviations. First, correlation (for numerical baseline variables) and t-test or ANOVA (for categorical baseline variables) will be used to determine relationships between individual baseline characteristics and summary (count) scores for the total number of abbreviations comprehended. Based on this preliminary analysis, multiple Poisson regression models may be used to predict summary comprehension scores using selected baseline characteristics ( $P < 0.15$  in the bivariate analyses).

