## 1.3. Study Objectives

The overall objective is to establish patient comprehension of abbreviations vs. expansions in clinical text, using several control mechanisms to isolate the main effect of expansion. This assessment is intended to:

- (1) characterize the extent of miscommunication due to abbreviations in health records;
- (2) evaluate the need for potential solutions such as automated abbreviation expansion.

We *hypothesized* that abbreviation expansion would improve patient comprehension of abbreviations in clinical text. As a secondary analysis, the study will determine associations between comprehension of abbreviations and common characteristics, including education level, socioeconomic status, and health literacy.

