| race                 | What race do you identify as?                      | 1 White
2 Black
3 Asian
4 Native American
5 Mixed
6 Other
7 Unsure/prefer not to answer |
| race_other           | Please specify "Other":                            | Text (required)                                                                                           |
| ethnicity            | What ethnicity do you identify as?                 | 1 Hispanic/Latino
2 Not Hispanic/Latino
3 Unsure/prefer not to answer                               |
| language_spoken      | What is your preferred language to speak?          | 1 English
2 Spanish
3 Cantonese
4 Mandarin
5 Russian
6 Other                               |
| languagespoken_other | Please specify "Other":                            | Text (required)                                                                                           |
| language_read        | What is your preferred language to read and write? | 1 English
2 Spanish
3 Cantonese
4 Mandarin
5 Russian
6 Other                               |
| language_read_other  | Please specify "Other":                            | Text (required)                                                                                           |

|                     |                                                                                                                               |                                                                                                                                                                                                                                     |
|---------------------|-------------------------------------------------------------------------------------------------------------------------------|-------------------------------------------------------------------------------------------------------------------------------------------------------------------------------------------------------------------------------------|
| education           | What is the highest level of education that you completed?                                                                    | 1 I have never attended school
2 Eighth grade
3 Some high school
4 High school
5 Some college
6 Associates degree
7 Bachelor's degree
8 Master's degree
9 Doctoral degree
10 Unsure/prefer not to answer |

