## 2.5. Randomization

Prior to launching recruitment, an independent statistician will randomly assign groups using a computer-generated block randomization algorithm of size 6. Groups will be assigned in a 1:1 ratio.

Two coordinators will enroll participants and collect data. REDCap will conceal each participant's allocation until directly after baseline data collection. Blinding after assignment is not possible due to the obvious nature of the intervention.

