### 3.2. Sample Size Calculation

Based on the clinician ratings, the estimated comprehension of expansions is 89% and the estimated comprehension of abbreviations is 56%. Therefore, we have anticipated a comprehension rate of 89% for the intervention and 56% for the control group. Our planned sample size of 60 patients will provide 80% power to detect this 33 percentage point difference in our primary outcome at the 5% significance level. We will stop recruitment once 60 participants have completed the trial.

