### 3.3. Main Analysis

We will use a two-sided unequal variances t-test with a significance threshold of  $P < 0.05$  to analyze differences in overall comprehension (primary outcome) between study groups based on a summary (count) score of the total number of abbreviated or expanded terms comprehended by the patient. Fisher's exact test of independence with a significance threshold of  $P < 0.05$  will be used to examine differences between abbreviated and expanded versions of each individual term. Uncertainty will be estimated using standard 95% confidence intervals.

We will conduct bivariate analyses to assess whether baseline characteristics differ by group. Nominal variables will be compared using Fisher's exact tests, while ordinal and numerical variables will be compared using Wilcoxon rank-sum tests. Participants will be analyzed according to their original allocation. One goal of the study design is to avoid missing data, and we do not anticipate having missing data. However, in the event of missing data, we will use multiple imputation methods. Analyses will be performed in R Version 3.6.3.

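### Section 3.4 has no class for ordinal predictors, so education and financial resources go to ANOVA, with a large loss of power for education if its nine levels are kept

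*Combined protocol and SAP*

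**What the plan says.** Section 3.4 looks for predictors of the abbreviation comprehension score among control participants only. It has two routes: correlation for numerical variables, and "t-test or ANOVA (for categorical baseline variables) will be used to determine relationships between individual baseline characteristics". Variables with P < 0.15 at this step may then enter Poisson regression models, which the plan makes optional.

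Section 3.3, on comparing baseline characteristics between arms, has a finer scheme. Nominal variables get Fisher's exact test, while "ordinal and numerical variables will be compared using Wilcoxon rank-sum tests". That scheme is not carried into 3.4.

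Section 1.3 sets the aim of the secondary analysis as associations with "common characteristics, including education level, socioeconomic status, and health literacy". Section 2.3 counts education, insurance type, financial resources and disability as socioeconomic. In Table 2.2, the education item ("What is the highest level of education that you completed") has nine ordered levels plus a tenth code for unsure or declined. Financial resources has three ordered levels, and each of the three health literacy items has five. No scoring rule is given for the literacy screener.

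**The concern.** Education and financial resources are stored as coded categories, so under the two routes in 3.4 they fall to ANOVA. ANOVA asks whether any level differs from any other. It spends one degree of freedom per level beyond the first and makes no use of the order. In an arm of about 30, nine levels cost eight degrees of freedom, for a question that is naturally about a gradient.

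Education is among the predictors that section 1.3 names, and the same P-values decide which variables reach the regression. At stake is the chance of detecting a real education gradient. Health literacy is a separate gap: the plan leaves open whether it is one score or three items, and that choice decides which test applies.

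**Working it through.** **The plan's own figure.** The documents state no power for the predictor analysis. The only power statement is for the primary outcome (section 3.2): 60 patients, 80% power, 89% against 56%. The pooled two-sided formula for two proportions gives

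n = [1.96·√(2·0.725·0.275) + 0.8416·√(0.89·0.11 + 0.56·0.44)]² / 0.33² = (1.238 + 0.494)² / 0.1089 ≈ 27.5, so 28 per arm.

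At 30 per arm the power is 83.4%, so the stated 80% is not reproduced exactly. That does not bear on this point; the section supplies only the sample size.

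**Inputs from the documents.**
- Control arm: "We will stop recruitment once 60 participants have completed the trial" (3.2) and "Groups will be assigned in a 1:1 ratio" (2.5), so 60/2 = about 30.
- Levels (Table 2.2): education 9, each literacy item 5, financial resources 3.
- Thresholds: 0.05, and the 0.15 screen in 3.4.

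**Assumed, not in the documents.** A linear monotone association with correlation r between level and score, r = 0.3 to 0.6, and all levels occupied.

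**Formula.** With R² = r², the noncentrality is λ = n·r²/(1 − r²). At r = 0.4, λ = 30·0.16/0.84 = 5.71. A trend test puts λ on 1 and 28 degrees of freedom. A k-level ANOVA spreads the same λ over k − 1 and 30 − k. At 0.05 the critical F is 4.20 for the trend (1, 28) and 2.42 for nine levels (8, 21). Power is the upper tail of the noncentral F.

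| Threshold | r | Trend | ANOVA, 9 levels | ANOVA, 5 levels | ANOVA, 3 levels |
|---|---|---|---|---|---|
| 0.05 | 0.3 | 38.4% | 13.8% | 20.5% | 28.9% |
| 0.05 | 0.4 | 63.6% | 24.5% | 37.8% | 51.3% |
| 0.05 | 0.5 | 86.3% | 42.8% | 62.3% | 76.7% |
| 0.05 | 0.6 | 97.7% | 68.6% | 86.5% | 94.5% |
| 0.15 | 0.4 | 81.8% | 46.9% | 61.0% | 72.8% |
| 0.15 | 0.5 | 95.2% | 67.2% | 82.0% | 90.5% |

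Losses at r = 0.4 and 0.05:
- education: 63.6 − 24.5 = 39.1 points
- one literacy item: 63.6 − 37.8 = 25.8 points
- finances: 63.6 − 51.3 = 12.3 points

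At the 0.15 screen they are 34.9, 20.8 and 9.0 points. Over r = 0.3 to 0.6 at 0.05, the education loss runs from 24.6 to 43.5 points.

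**Check by simulation.** Control arms of 30 were simulated with a score of mean 5.6 and SD 2, rounded and held to 0-10. Assumed level shares were 1/5/8/22/18/10/20/12/4% for education, 40/20/20/12/8% for a literacy item and 25/50/25% for finances. At r = 0.4, with power at 0.05 first and passing the 0.15 screen second:
- Education: ANOVA 26% and 49%, Spearman 57% and 77%.
- Literacy item: ANOVA 36% and 58%, Spearman 56% and 76%.
- Finances: ANOVA 48% and 69%, Spearman 58% and 77%.

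With no true association, both tests reject at about 5% and 15%, so the ordered test does not gain power through a higher false-positive rate.

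**Fewer education levels.** With r held at 0.4, ANOVA power at 0.05 is 30% with seven levels, 38% with five and 51% with three, against 64% for a trend.

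**The case against.** The strongest case on the other side is that this is a gap in wording, with a serious cost for one variable only. Much of that stands.

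- **Health literacy.** A reader might infer that all the named predictors are sent to ANOVA. The documents do not settle this. Section 2.3 uses the screener to estimate one construct, and all three items run from 1 to 5 in the same direction, so they can be summed. A summed score is numerical and would go to correlation, with no loss.
- **Thresholds.** A reader might also infer that real gradients will probably miss both 0.05 and the 0.15 screen. That fits at most nine-level education at r of about 0.4 or below. At r = 0.5, education passes the screen about 67% of the time. The small arm limits any test: at r = 0.4, Spearman itself misses 0.05 in about 43% of samples (100 − 57).
- **Other socioeconomic variables.** Insurance type is nominal and disability is yes/no, so t-test or ANOVA suits them.
- **Merging.** The plan does not fix the number of education groups. With education merged to three, simulation at r = 0.4 gives ANOVA 42% and 65% against Spearman 56% and 77%, a gap of 12-14 points. But merging is not in the plan either, and the loss shrinks without vanishing.
- **Stakes.** The analysis is secondary and exploratory, no power is claimed for it, and the Poisson model is optional.

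**Conclusion.** The point holds within limits. Section 3.4 omits a class of variable that 3.3 recognizes, and its literal reading sends education and financial resources to a test that ignores order. The loss is large for education at nine levels: about 25% power instead of 57-64% at 0.05, and 47-49% instead of 77-82% at the screen, for r = 0.4. It is material for a literacy item used singly (20-26 points at 0.05) and modest for finances (8-12 points over both thresholds).

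These sizes rest on about 30 control patients, a monotone association and, for the simulation, assumed level shares. Merged or empty levels reduce the loss, and a non-monotone relation could reverse it. The documents do not support concluding that the secondary question would be answered wrongly because of the test, or that the primary comparison is affected. It is worth correcting because the correction is nearly free and also settles how health literacy is scored.

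**What to change.** In section 3.4, state the following:

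- Use Spearman rank correlation for numerical and ordinal predictors: age, education levels 1-9, financial resources, and the sum of the three health literacy items (range 3-15).
- Keep t-test or ANOVA for nominal variables only.
- Enter each ordinal predictor in any regression as a single trend term.
- Education code 10 is not an ordered level. Treat it as missing and handle it under the multiple imputation rule in section 3.3.
- Show mean scores by level for each ordinal predictor.

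The cost is a few sentences and no new data. The downside is that a rank correlation can miss a non-monotone pattern, and the table of means is there to reveal one.

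### Screening baseline characteristics at P < 0.15 and refitting in the same 30 or so control patients leaves a substantial, uncontrolled risk of false predictors in the secondary analysis

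*Combined protocol and SAP*

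**What the plan says.** Section 1.3 sets a secondary aim: "the study will determine associations between comprehension of abbreviations and common characteristics, including education level, socioeconomic status, and health literacy". Section 3.4 carries it out: "We will conduct a subgroup analysis of control group participants to assess potential predictors of objective comprehension of abbreviations". The first step uses correlation for numerical variables and a t-test or ANOVA for categorical ones, "to determine relationships between individual baseline characteristics and summary (count) scores for the total number of abbreviations comprehended". The second step is conditional: "Based on this preliminary analysis, multiple Poisson regression models may be used to predict summary comprehension scores using selected baseline characteristics", where selected means P < 0.15 in the first step.

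The section gives no closed list of candidates, no multiplicity correction, no internal validation or shrinkage, no limit on model size and no significance threshold for the Poisson model. It does not guarantee a place in the model for any characteristic named in section 1.3. The analysis is called secondary but is not labelled exploratory.

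**The concern.** The same patients choose the variables and then test them. A variable enters the model because its association in this sample happened to be strong, so its P value and interval in the refitted model are too favourable unless the selection is allowed for. With few patients and many candidates, chance alone will usually put something into the model. The screen also works against real predictors: it can discard a characteristic the study set out to examine, and it exaggerates the coefficients of those that survive.

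At stake is the answer to the secondary question of which patients struggle with abbreviations. The comparison of abbreviations with expansions does not depend on it.

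**Working it through.** **Plan's own figure.** The documents give no figure for the predictor analysis. The stated power for the main comparison (80% with 60 patients, 89% against 56%, two-sided 5%) can be reproduced. The mean rate is (0.89 + 0.56)/2 = 0.725 and SD = √(0.725 × 0.275) = 0.4465. A two-sample t-test then needs 29.7 per arm, so 30, with power 80.4%.

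**Inputs.**
- Control patients: section 3.2 says "We will stop recruitment once 60 participants have completed the trial" and section 2.5 says "Groups will be assigned in a 1:1 ratio". This gives 60/2 = 30, a derived number.
- Candidates: the text of section 2.3 names nine demographic and socioeconomic characteristics plus health literacy, so 10. Table 2.2, with separate spoken and read language, insurance status and type, disability and its type, and three literacy items, gives 15. The plan states neither number.
- Screen: P < 0.15 (section 3.4).
- Final-model threshold: 0.05, an assumption.
- Score: 10 terms, with the clinician-estimated rates for abbreviations in Table 2.3.

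**Step 1: the screen, all candidates null and independent.** Expected passes = 0.15k. P(at least one) = 1 − 0.85^k.
- k = 10: 1.5 expected; 1 − 0.85^10 = 80.3%.
- k = 15: 2.25 expected; 1 − 0.85^15 = 91.3%.
- Candidates correlated at 0.3 (assumption, simulated): 73% to 85%.

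At the bivariate step, at least one P < 0.05 has probability 1 − 0.95^10 = 40.1% to 1 − 0.95^15 = 53.7%, or 33% to 48% in simulation at correlation 0.3.

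**Step 2: screen, then refit.** Simulated with n = 30, ten items at the Table 2.3 abbreviation rates, noise predictors, and 10 or 15 candidates.

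With dispersion-scaled standard errors, at least one false predictor at P < 0.05 appears in 29% to 44% of trials (independent candidates) or 19% to 26% (correlated at 0.3). With independent candidates, each noise variable that passes the screen is significant about 24% to 31% of the time rather than 5%.

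With plain Poisson standard errors the result turns on the variance-to-mean ratio of the score. If patients did not differ in ability, the Table 2.3 rates give mean Σp = 5.58 and variance Σp(1 − p) = 1.588, a ratio of 0.28. Poisson assumes 1. For independent candidates:

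| Variance/mean | At least one false predictor |
|---|---|
| 0.28 | 0.1% |
| 0.64 | 9–10% |
| about 1.0 | 29–34% |
| about 1.3 | 50–57% |

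**Step 3: effect on real predictors.** At n = 30 a variable needs an observed correlation of about 0.27 in absolute value to pass. If the true correlation is 0.3, it is dropped 42% of the time, and when kept its mean estimate is 0.41. If the true correlation is 0.2, it is dropped 64% of the time, and when kept its mean estimate is 0.37. The correlations of 0.2 and 0.3 are assumptions. This step does not need the other candidates to be null.

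**The case against.** The case for leaving the plan alone is that the model is optional, the analysis is secondary and speaks only of potential predictors, and no threshold is set for calling a term significant. All of that is true, and it limits the weight of the point.

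A reader might infer more than the documents support, in four ways.

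- **That false predictors are likely to be reported.** With correctly scaled errors, every final-model rate above is below one half. With plain Poisson errors the rate can be negligible, because a score bounded at 10 may vary less than a Poisson count. Some candidates, such as education and health literacy, may be real predictors, which leaves fewer nulls. The inference would hold if every variable passing the screen were presented as a predictor, which the plan neither says nor excludes.
- **That a linear-model simulation gives the size.** It yields about 36% for 10 and 42% for 14 independent null variables, falling to 21% to 25% at correlation 0.3. The plan specifies Poisson, so no single figure stands for it.
- **That screening alone causes the excess.** Ten unscreened tests at 0.05 already give 40%. What screening adds is the optimistic P value for each selected variable and the loss or inflation of real effects.
- **That education must go to ANOVA over ten codes.** Section 3.4 mentions only numerical and categorical variables, while section 3.3 treats ordinal ones separately. ANOVA is one reading; the gap is that ordinal items have no assigned method.

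The list in section 1.3 is also open-ended, and socioeconomic status is a domain rather than a variable. None of this supplies a safeguard. Error rates that vary so widely with unstated choices are a reason to state the choices.

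**Conclusion.** The point holds as a substantial, uncontrolled risk of false predictors in an optional secondary analysis. If all 10 to 15 candidates were null, at least one would pass the screen with probability 80% to 91% (73% to 85% if correlated at 0.3). A false predictor at P < 0.05 would follow in 19% to 44% of trials with correctly scaled errors, and in anything from near 0 to over 50% with plain Poisson errors. These figures rest on 30 control patients, wholly null candidates, an assumed 0.05 threshold and, for plain Poisson, a between-patient spread the documents do not give. Separately, the rule can remove education, socioeconomic status or health literacy from the model, and it overstates the effects it retains. A change is worth making because it is cheap.

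**What to change.** In section 3.4:

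- Delete the P < 0.15 screen.
- Pre-specify one control-arm model with three terms: the health-literacy sum score, education as an ordered score, and one socioeconomic measure fixed in advance. Section 2.3 lists four socioeconomic characteristics, one of which is education; financial resources is one possible choice among the others.
- Name a model suited to a count bounded at 10, with dispersion-scaled or robust standard errors, for example quasi-binomial.
- Report all three terms with 95% intervals whatever their P values.
- State that ordinal items are analysed as ordered scores.
- Label all other associations exploratory and report them descriptively.

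The cost is SAP wording; no new data or patients are needed. There are two downsides. An unexpected predictor outside the three would be described, not tested. Three unadjusted terms still carry a family-wise error of about 1 − 0.95^3 = 14%, which a Holm or Bonferroni correction would hold to at most 5% if significance claims are wanted.

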## 2.4. Intervention

This study is designed to compare comprehension of abbreviations vs. expansions in clinical text. We have used the following process to identify abbreviations for inclusion in the randomized trial:

- Using the Clinical Abbreviation Recognition and Disambiguation (CARD) framework, we identified the 20 most common abbreviations found in advanced heart failure notes, excluding those abbreviations judged as highly obscure by participating clinicians (n=6).
- Participating clinicians rated these 20 abbreviations and their corresponding expansions as easy, moderate, or difficult for patients to comprehend. We then choose 10 of the 20 abbreviations of varied difficulty and their corresponding expansions for inclusion in the randomized trial.

**Table 2.3** displays the included abbreviations and corresponding clinician ratings.

| Table 2.3. Clinician Perceptions of Patient Comprehension of Abbreviations |                                 |                                            |                                                                                                 |
|-----------------------------------------------------------------------------------|---------------------------------|--------------------------------------------|-------------------------------------------------------------------------------------------------|
| Clinical Text                                                                     | Difficulty Score
(out of 12) | Estimated Comprehension
(% of patients) | Interpretation                                                                                  |
| Abbreviations                                                              |                                 |                                            |                                                                                                 |
| hrs                                                                               | 0                               | 100%                                       | [figure not shown] Easy        |
| MD                                                                                | 1                               | 92%                                        | [figure not shown] Easy        |

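### Section 3.4 names Poisson regression, with no dispersion correction, for a score bounded at 10; its standard errors are probably too wide in the optional multivariable step

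*Combined protocol and SAP*

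**What the plan says.** Section 3.4 looks in the control group for baseline characteristics that go with understanding abbreviations. It has two steps. The first relates each characteristic to the score by correlation, t-test or ANOVA. The second is optional: for characteristics with P < 0.15 in the first step, "multiple Poisson regression models may be used to predict summary comprehension scores using selected baseline characteristics".

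Section 3.3 defines the outcome as a "summary (count) score of the total number of abbreviated or expanded terms comprehended by the patient". Section 2.4 fixes its ceiling: "We then choose 10 of the 20 abbreviations of varied difficulty and their corresponding expansions for inclusion in the randomized trial". The possible values are therefore 0 to 10.

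The plan names no other multivariable model. It mentions no dispersion check, quasi-likelihood or robust standard error, and gives no standard deviation for the score and no correlation between a patient's answers. The Synopsis and section 1.3 both list the predictor analysis as secondary.

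**The concern.** A Poisson model describes an open-ended count whose variance equals its mean. A sum of ten yes/no items has a ceiling, and its variance depends on how easy each item is and on how strongly answers cluster within a patient. Unless clustering is strong, that variance is smaller than the mean. An uncorrected Poisson model then reports standard errors that are too large, intervals that are too wide and P values that are too high.

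The two steps of section 3.4 would also disagree. A characteristic can pass a correlation or t-test that uses the observed spread, then look null in the adjusted model because that model imposes a larger spread. With about 30 control patients (60 randomized 1:1), there is little power to give away.

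**Working it through.** **Inputs.** Table 2.3 gives difficulty scores out of 12 for the ten abbreviations: 0, 1, 3, 3, 5, 5, 6, 9, 10, 11. The estimated comprehension rate is p = 1 − score/12.

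**The plan's own figure.** The scores sum to 53, so the expected number correct is 10 − 53/12 = 5.58, or 56%. This reproduces the control rate in section 3.2: "we have anticipated a comprehension rate of 89% for the intervention and 56% for the control group". The 80% power stated there concerns the primary comparison and has no bearing on this point.

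**Variance with independent answers.** Σp(1 − p) = Σ score × (12 − score)/144 = (0 + 11 + 27 + 27 + 35 + 35 + 36 + 27 + 20 + 11)/144 = 229/144 = 1.59. The variance-to-mean ratio is 1.59/5.58 = 0.28. For weak predictors, the Poisson standard error divided by the correct one is about √(mean/variance) = √(5.58/1.59) = 1.87.

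**Variance with correlated answers.** The correlation is an assumption, so a range is shown. Hold the Table 2.3 rates fixed and let each answer be a latent normal variable cut at z = Φ⁻¹(p), with common correlation ρ within a patient. The variance is Σp(1 − p) + 2Σ[Φ₂(zᵢ, zⱼ; ρ) − pᵢpⱼ], summed over pairs.

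| ρ (assumed) | Variance | Poisson SE / correct SE |
|---|---|---|
| 0 | 1.59 | 1.87 |
| 0.1 | 2.22 | 1.58 |
| 0.2 | 2.86 | 1.40 |
| 0.3 | 3.49 | 1.26 |
| 0.4 | 4.12 | 1.16 |
| 0.5 | 4.76 | 1.08 |
| 0.6 | 5.39 | 1.02 |
| 0.7 | 6.03 | 0.96 |

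The direction reverses between 0.6 and 0.7. In terms of score reliability, variance equals mean when KR-20 = (10/9)(1 − 1.59/5.58) = 0.79. A random-person logit model crosses at about the same place: variance 5.16 at person SD 2 and 5.81 at SD 2.5. The largest variance possible with these rates is 7.91, a ratio of 1.42 to the mean.

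**Consequence by simulation.** All runs use n = 30, a 5% two-sided level and model-based Poisson errors. Section 3.4 states neither the level nor the type of error for this model, so both are assumptions, as are the effect sizes.

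One predictor, probit slope 0.3 per SD, 2,000 replicates:

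| ρ | Power, Poisson | Power, quasi-binomial | Type I error, Poisson | Type I error, quasi-binomial |
|---|---|---|---|---|
| 0 | 36% | 90% | 0% | 5.2% |
| 0.3 | 43% | 59% | 1.1% | 4.8% |
| 0.5 | 46% | 47% | 2.8% | 4.0% |

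A separate run used a binary predictor (15 v 15), a true difference of 1.5 points, the logit model and 3,000 replicates. Power for Poisson v quasi-Poisson was 34% v 89% at dispersion 0.28, 39% v 60% at 0.57, 40% v 49% at 0.76, and 41% v 37% at 1.04.

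The step that section 3.4 actually assigns to Poisson is the adjusted model. With two predictors fitted together, Poisson power was 23%, 33% and 36% at ρ = 0, 0.3 and 0.5, against 79%, 55% and 41% for a linear model using the observed variance. Poisson Type I error was 0–4%.

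**The case against.** The strongest reply has four parts.

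*The variance is unknown.* This stands. A reader might infer from the ceiling alone that the variance is well below the mean. The documents do not show that: they give no standard deviation, the rates are clinicians' estimates, and an analysis that looks for traits such as education and health literacy expects some clustering of answers within patients. At ρ = 0.5 the single-predictor loss is trivial (46% v 47%), and beyond about 0.6 the errors become too narrow. One consideration pulls the other way: the regression depends on the residual variance after predictors, which is smaller than the total.

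*The first step already finds single predictors.* This also stands. Correlation, t-test and ANOVA use the observed variance. In the slope-0.3 scenario, the planned correlation test at 5% has power of 88%, 59% and 48% at ρ = 0, 0.3 and 0.5, and the predictor passes the P < 0.15 screen in 96%, 77% and 69% of datasets. A reader might therefore infer that real predictors will go unnoticed under this plan. That goes too far; what is lost is power in the adjusted step. The two-predictor figures show that this loss remains after the objection is granted.

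*The step is optional and secondary.* True, and it limits the weight of the point. But Poisson is the only multivariable model that the plan names.

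*Fitted means above 10 are rare.* In simulation with the 0.3 slope, a fitted mean exceeded 10 in only 0.3–2.7% of datasets. That possibility is a minor reason to change the model.

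**Conclusion.** The point holds in a limited form. The Poisson variance assumption does not suit a 0–10 sum of yes/no items, and section 3.4 has no correction for it. The model-based standard errors are probably too wide, by a factor between 1.87 (independent answers) and about 1.02 (latent correlation 0.6). With stronger clustering they are too narrow. In the adjusted step, the power loss runs from severe (23% v 79%) at correlation 0 to slight (36% v 41%) at 0.5.

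These sizes rest on the Table 2.3 ratings, an assumed correlation range, assumed effect sizes and model-based errors. The primary Welch t-test, the per-term Fisher tests and the bivariate screen are not affected.

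**What to change.** In section 3.4, replace Poisson regression with a model whose dispersion is estimated from the data. The preferred choice is logistic regression for terms correct out of 10, with quasi-binomial dispersion and t-based intervals, because it also keeps predictions between 0 and 10. Quasi-Poisson or linear regression would also correct the standard errors; in the binary-predictor run, quasi-Poisson held its Type I error at 4.4–5.4%. An estimated dispersion corrects the errors in either direction, so the change does not depend on guessing the correlation.

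The cost is one sentence and a standard R function. No new data and no change to the sample size are needed.
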